### Data Analysis

We will collect demographic information from the participants for the study. We will compare baseline variables, such as essential participant characteristics, primary, and secondary end points, to summarize the differences between the 2 groups at the start of the study (T1). For the analysis of categorical data and continuous data, the chi-square test and 2-tailed *t* test will be used. We use R (version 4.1.2; R Foundation) for data analyses, with a significance level of *P*=.05.

Aim 1 is to examine the effects of the technology-based PEER intervention on fall risk, dynamic balance, and accelerometer-based PA.

The hypotheses are as follows:

*H 1.1*: The PEER group will reduce the fall risk compared with the control group.*H 1.2*: The PEER group will improve the dynamic balance compared with the control group.*H 1.3*: The PEER group will improve accelerometer-based PA compared with the control group.

Data will be analyzed according to the intention-to-treat principle [100]. We will model the fall risk, dynamic balance, and accelerometer-based PA as longitudinal outcomes consisting of 4 measurements (baseline or T1, after program completion or T2, follow-up at 3 months or T3, and follow-up at 6 months or T4) using the longitudinal linear mixed model (LMM) [101]. The LMM allows all low-income older adults and their available data to be included in the analysis, even for unequal group sample sizes, and the group heterogeneity can be addressed in the variance structure of random effects. It is hypothesized that the PEER group will show improvement in all outcome measures over time. To test hypothesis *1.1*, between-arm differences for fall risk scores, the likelihood ratio test (LRT) [101] associated with LMM will be used from all follow-up assessment visits. Similarly, the LRTs will be used to test hypotheses *1.2* and *1.3* for between-arm differences for dynamic balance and PA, respectively. The CDC-recommended scoring scheme will be adopted to process fall risk, TUG, and STS data [102]. For example, the average score of the number of STS repetitions a person can complete is based on different age and sex groups [102].

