*H 2.1*: The PEER group will have a more adaptive shifting compared with the control group.*H 2.2*: The PEER group will have a more positive shift in their perceptions of aging compared with the control group.

To test hypothesis *2.1* (FRA shifting), the 4 FRA quadrants will be determined by grid coordinates based on 2 continuous level measures (BBS and short FES-I scores). We will classify shifting into 2 types: maladaptive and adaptive shifting. Adaptive shifting is moving from irrational, incongruent, or congruent to rational. The outcome is a percentage of low-income older adults with baseline (T1) in irrational, incongruent, or congruent quadrants who end up in the rational quadrant after program completion (T2). Maladaptive shifting is a movement from rational to any other quadrant, and the percentage of low-income older adults will be calculated. After program completion (T2), the baseline FRA categories (T1) may remain the same or shift to a different FRA category. We will form a 4×4 contingency table for the 4 FRA categories at each follow-up time point (T3 and T4) to summarize the shifts. The standard 4×4 table analysis will be performed to examine the FRA shifting, either using a chi-square test or exact test, depending on the actual counts observed in the 4×4 table. The BBS and short FES-I scores will be collected in 4 planned visit time points (T1, T2, T3, and T3). We will use the Generalized Linear Mixed Model (GLMM) to analyze these 2 end points for assessing the difference between the PEER intervention and control arms on the shift of FRA categories [109]. Our longitudinal data on the PEER effects of different types of shifting on low-income older adults will contain repeated binary measures of the shifting status over time. The binomial GLMM with the logic link will allow us to assess the difference between the 2 arms in FRA shifting, and the associated LRT [101] will be used to test hypothesis *2.1* if a significant adaptive shifting is detected in the PEER group compared with the control group. The GLMM can address the group heterogeneity by specifying the corresponding covariance structure in random effect terms.

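### The chi-square or exact test of the 4×4 FRA table tests independence of quadrants, not shifting or an arm difference; keep the table as a descriptive display

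*Protocol article*

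**What the plan says.** All of this is in the protocol article, Data Analysis, in the text for Aim 2.

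- Hypothesis 2.1 is a comparison between arms: "The PEER group will have a more adaptive shifting compared with the control group".
- Adaptive shifting is measured among people outside the rational quadrant at baseline "who end up in the rational quadrant after program completion (T2"). Maladaptive shifting is a move out of the rational quadrant.
- After the program, "the baseline FRA categories (T1) may remain the same or shift to a different FRA category".
- The table: "We will form a 4×4 contingency table for the 4 FRA categories at each follow-up time point (T3 and T4) to summarize the shifts".
- The test on it: "The standard 4×4 table analysis will be performed to examine the FRA shifting, either using a chi-square test or exact test". Observed counts decide between the two.
- A separate model: "The binomial GLMM with the logic link will allow us to assess the difference between the 2 arms in FRA shifting". Its likelihood ratio test is the one named for hypothesis 2.1.

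The significance level is .05 throughout. No paired or symmetry test is named for the table, and the table is given no arm dimension.

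**The concern.** A four-by-four table of the same four categories that summarizes shifts from baseline has, on the natural reading, the T1 quadrant on one axis and the follow-up quadrant on the other. A table comparing arms would be two by four.

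The standard chi-square or exact test of such a table asks whether follow-up quadrant is independent of baseline quadrant. Measured twice, the same people resemble themselves, so the counts pile up on the diagonal and independence is rejected. A small p-value then mostly reflects people who did not shift. The test also has no term for arm.

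At stake is how the result reads. The test sits under hypothesis 2.1 and is described as examining shifting. A very small p-value is likely whether or not PEER works, and it could be presented as evidence of shifting.

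There is also a timing mismatch. The adaptive-shift outcome is defined at T2, but the tables are planned only "at each follow-up time point (T3 and T4) to summarize the shifts", so the defining time point has no table.

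**Working it through.** The plan gives no operating figure for the 4×4 test, so there is none to reproduce. The check is what the test does when PEER has no effect.

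**Inputs**

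- From the article: alpha .05 (Data Analysis); 120 completers per arm, 170 enrolled per arm and about 40% dropout (Power Analysis and Sample Size). Applying the dropout to enrollment gives 170 × (1 − 0.40) = 102 per arm, so 102 and 120 are both used.
- Assumed, not in the article: how stable a person's quadrant is over time, the shares of people in each quadrant, and no clustering by site.

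**1. Direction of the statistic (one arm of 120)**

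Let a fraction k of people keep their quadrant and let the rest be redistributed according to the overall quadrant shares. There is then no net shift. For a table with four categories the expected-count statistic is

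X² = n × k² × (4 − 1), on 9 degrees of freedom.

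- Nobody moves (k = 1): 120 × 1 × 3 = 360, p about 5 × 10⁻⁷².
- k = 0.5: 120 × 0.25 × 3 = 90.
- k = 0: X² = 0.
- 60% finish in the rational quadrant whatever their baseline: X² = 0, p = 1.

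Now start from k = 0.5 with equal quadrant shares, and move an additional share of each non-rational group to rational:

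| Additional share moved to rational | X² |
|---|---|
| 0% | 90 |
| 10% | 71 |
| 20% | 57 |
| 40% | 35 |

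In this setting the statistic falls as the desired shift grows.

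**2. Rejection with no true change, correlated scores (one arm)**

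Two normal scores, standing for BBS and short FES-I, are each cut in two to form the quadrants at T1 and at follow-up. Each has within-person correlation ρ and no mean change. Test at 5%.

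| ρ | Rejection, n = 102 to 120 |
|---|---|
| 0 | about 5% |
| 0.3 | about 38% to 54% |
| 0.5 | about 94% to 98% |
| 0.7 and 0.8 | 100% |

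The ranges cover both sample sizes and cuts away from the median.

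**3. Rejection with no PEER effect, persistence model of step 1**

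Both arms share the same transitions, with 120 per arm, three sets of quadrant shares (12% to 35% rational) and 1,000 runs per setting.

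| k | 4×4 chi-square, PEER arm (120) | 4×4 chi-square, arms pooled (240) |
|---|---|---|
| 0 | 4% to 6% | 4% to 6% |
| 0.1 | 22% to 26% | 39% to 42% |
| 0.2 | 72% to 75% | 96% to 98% |
| 0.3 | 97% to 99% | 100% |
| 0.5 and above | 100% | 100% |

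In the same runs, Stuart-Maxwell in the PEER arm rejected in 3.3% to 6.0%. A 2×2 comparison of adaptive shifting between arms, among those non-rational at baseline, rejected in 3.5% to 6.1%. Both are near the nominal 5%.

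**The case against.** **Hypothesis 2.1 has its own test.** A reader might infer that the 4×4 test is what decides hypothesis 2.1, leaving it without a valid test. The article does not support that. The same paragraph names a between-arm binomial GLMM with a likelihood ratio test for that hypothesis. This objection stands in full and limits the harm to an ancillary p-value.

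**The table is meant as a summary.** Its stated purpose is to summarize shifts, and nothing says how the p-value will be interpreted. That is fair as to the table, and misreporting is a risk rather than a stated plan. But the next sentence attaches an inferential test and says it examines shifting, so the choice of test is fixed in the text.

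**The axes are inferred.** The article does not say that rows are T1 and columns follow-up, nor whether tables are built within arm. This stands as a limit on certainty. Building the tables within each arm would not change the fault, as step 3 shows for one arm.

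**Significance is not guaranteed.** A reader might also infer that the test must come out significant. It need not: rejection is about 5% with no stability and well short of certain when stability is weak. The pilot figures in Principal Findings (PEER: 11% adaptive and 5.3% maladaptive shifts among 19 people) are consistent with high stability. They do not give the full transitions, and up to 32% of the pilot control group shifted maladaptively.

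**Much of the remedy is already planned.** The between-arm model and the two kinds of shift are in the text. What remains is to remove or replace one test and to align the time points.

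**Conclusion.** The point holds for the test as written, on the natural baseline-by-follow-up reading. The chi-square or exact test addresses independence, detects mainly persistence, contains no arm comparison, and tends to weaken as movement to the rational quadrant increases.

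The near-certain rejection under no change is conditional on ordinary stability, meaning a correlation of at least 0.5 on both scores. That assumption is not a figure from the article.

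Severity is moderate. The outcome is secondary, the test is ancillary, and no primary result, sample size or formal conclusion on hypothesis 2.1 depends on it. It should still be corrected, because the p-value is uninformative about shifting and easily mistaken for support.

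**What to change.** - Delete the chi-square or exact test of the 4×4 table. Present the tables descriptively, with T1 quadrant in rows and follow-up quadrant in columns, separately by arm, at T2, T3 and T4.
- If net movement within an arm is to be tested, name a test for paired categories: Stuart-Maxwell for a change in the quadrant distribution, or Bowker for symmetry. Label it as within-arm and not as a test of hypothesis 2.1.
- State that the between-arm binomial GLMM, accounting for site as the unit of randomization, is the only test of hypothesis 2.1.

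Cost: one or two sentences in the analysis section and no new data, since BBS and short FES-I are already collected at every planned visit.

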### Rationale

A qualitative approach will allow us to explore the complex, multilevel pathways through how the PEER intervention affect at individual and peer-group levels. We may also identify barriers to successful FRA adaptation and barriers to access and adoption of the technology-based intervention that cannot be identified in quantitative data but will be important to consider in the future. Interviews with participants will provide insights into the variability across settings and implementation factors that will be instructive for program and policy planning. Importantly, interviews will amplify the voices of low-income individuals who traditionally hold less power in program planning [110].

### Design and Sample

We will use in-depth, one-on-one, semistructured interviews with up to 30 participants from the PEER after the completion of the intervention (T2). Semistructured interviews will help ensure that key concepts are addressed while allowing flexibility to adjust and rearrange questions to maximize interview flow and useful data collected. Theoretical sampling will help us gain the perceptions we need in terms of demographic and experiential variation [111,112]. We will sample until saturation of themes and content has occurred. The interviews (30-40 minutes) will be conducted by a trained interviewer either in person or by phone or web conferencing and will be audio recorded. The COREQ (Consolidated Criteria for Reporting Qualitative Research) [113,114] will be used during all phases of the process to optimize quality.

### Interview Guide

The National Institute on Minority Health and Health Disparities research framework [115] will help inform the development of the interview guide and focus on the (1) three domains of influence (biological, behavioral, and sociocultural) and (2) two levels of influence (individual and peer groups) that are most relevant to participant experiences and intervention evaluation. Interview questions will focus on their experience of participating in the PEER intervention, acceptability of PEER, potential barriers to accessing and adopting PEER in the community, and recommendations for future work. Consistent with the standard qualitative methodology, interview guides will be pilot-tested and adjusted based on findings from early interviews [116].

### Analysis

Data will be analyzed based on the analytic process of interpretive description, which is used to develop findings for clinical practice [117,118]. VL (coinvestigator) and the PI will generate initial codes focusing on participants’ experiences with PEER and will meet to establish consensus on the coding and using the NVivo software (version 12; QSR International) to aid in sorting and organizing the data. Consistent with the interpretive description, we will maintain an open stance toward coding to understand participant experiences [118]. Coding will continue until no new information is forthcoming from the data and the categories appear “saturated” [112]. Field notes will be coded to aid data interpretations and provide context, as they will contain interviewers’ impressions and observations during the interviews [111]. We will collate codes into themes, review them for their fit to the data, and categorize and label themes. We will conduct initial analyses on all data as soon as they are collected to allow for theoretical adjustments to the questions and guide sampling strategies for future interviews.

### Domains of Quality

We will enhance quality via the following strategies:

Maximal variation in sampling by ensuring variability on the factors that likely influence participants’ experience (age and context). We will enhance the credibility of the data and seek out a range of responses to the PEER, both positive and negative.Throughout the study, we will document all the methodological decisions and the reasoning behind them to maintain an accurate audit trail and ensure interpretive rigor [111].After identifying general themes and subthemes in the qualitative data analysis process, the entire research team will review and discuss a summary through peer debriefing [119].We will encourage team members who are not directly involved in the analysis to provide feedback and ask critical questions about the methods, decisions, and interpretation.Inference transferability will provide a description of the participants to allow for transferability of findings to similar settings, contexts, and people [120].

### Ethical Considerations

The Institutional Review Board of the University of Central Florida granted ethics approval for this study (protocol STUDY00003206) on October 14, 2022. All participants will receive information before participation.

## Results

As of August 2023, the enrollment of participants is ongoing.

## Discussion

### Principal Findings

Our developed PEER intervention is focused on providing physio-feedback using technology, promoting cognitive reframing, enhancing peer-led exercises, and incorporating exercises into daily activities. We aimed to examine the effectiveness of the technology-based PEER intervention on 3 primary outcomes (fall risk, dynamic balance, and accelerometer-based PA) and 2 secondary outcomes (FRA shifting and negative self-perceptions of aging). We hypothesized that the PEER group will reduce the fall risk, improve the dynamic balance, and improve accelerometer-based PA compared with the control group.

Our pilot study found that the PEER intervention (n=19) had a significant reduction in the CDC fall risk score from preintervention to postintervention (effect size Cohen *d*=0.6; *P*=.02) [32]. We also found that the PEER group had significant improvement in the TUG (*P*=.001; Cohen *d*=1.0) and STS (*P*<.001; Cohen *d*=0.95) tests [32]. In addition, in a pilot study [77], 11% of participants in the PEER group (n=19) had adaptive shifting compared with none in the control group (n=22). Up to 32% of the participants in the control group had maladaptive shifting compared with only 5.3% in the PEER group [77].

Existing fall prevention intervention technologies do not enable participants and practitioners to interact and collaborate [44] even with technologies that bring viable strategies to maintain PA, prevent disability, and increase access to quality care. The physio-feedback using portable technology is a vital component of the PEER intervention for screening fall risk at home or in their communities and initiating a fall risk communication between older adults, their caregivers, and practitioners. The physio-feedback and cognitive reframing strategies improve older adults’ competence by aligning their physiological fall risk with FOF or body and mind and increasing their fall risk awareness [116]. Few studies focused on improving PA in socioeconomically disadvantaged groups [121] despite recommendations for action on the social determinants of health for improving PA. Regular PA improved quality of life and reduced fall risk and mortality [122]; however, a lack of motivation to participate in PA is a crucial barrier. The peer-led exercises with peer coaching strategies may help build a connection and increase the motivation to participate in PA for older adults [50].

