### Power Analysis and Sample Size

The sample size estimate was based on the primary outcomes of fall risk (CDC fall risk score) and PA (normalized MVPA) for aim 1 and the secondary outcome of FRA shifting (BBS score) for aim 2. The difference in the normalized mean MVPA between the PEER group (mean 3.67, SD 2.54) and the control group (mean 5.38, SD 2.68) and the difference in the fall risk score between the PEER group (mean 2.72, SD=3.23) and the control group (mean 2.21, SD=2.06) are considered markers of PA and fall risk, respectively. Considering a clinically relevant normalized difference in MVPA of 1.7 (SD 2.60) and a fall risk score difference of 0.50 (SD 2.56), the medium effect size Cohen *d*=0.25, intraclass correlation (ICC) of 0.8, and a significance level of are used for the calculation of the sample size. A sample size of 120 participants per arm is needed to reach 80% statistical power to detect the difference between the PEER and control groups on repeated measures of normalized MVPA. A sample size of 120 participants per arm is needed to reach 80% statistical power to detect the difference between the PEER and control groups on repeated measures of normalized MVPA.

In addition, the sample size was also based on the following: (1) at least 3 sites per arm; (2) an initial hypothesis that at least 10% (34/340) of the irrational, incongruent, and congruent FRA would shift to rational FRA after PEER completion; (3) an approximate study adherence rate of 80% [56], and (4) an estimated study dropout rate of approximately 40% (136/340) over time. Therefore, the sample size was increased from 120 to 170 per arm, resulting in a total of 340 participants. On the basis of our pilot study [26], we estimate that approximately 60% (204/340) of the low-income older adults will meet all inclusion and exclusion criteria and will be interested in participating in this study. We estimate that a minimum of 567 low-income older adults will be screened to identify 340 low-income older adults for enrollment, and approximately 240 low-income older adults (120 per arm) are needed to complete the study. Given the sample size of 120 per arm, a significance level of *P*=.05, and 80% power, considering a clinically relevant BBS mean score difference of 8 (SD 12), the effect size Cohen *d*=0.36 can be achieved to compare the intervention effect based on secondary outcomes.

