##### Dynamic Balance

*Dynamic balance* will be assessed using the “Timed Up and Go” (TUG) and “Sit to Stand” (STS) tests suggested by the CDC [2] and the American Geriatric Society [65]. It is important to conduct >1 balance test, as some participants may be identified as at risk on one and not another [64]. The TUG test is a commonly used method for evaluating functional mobility and predicting the risk of falling [66,67]. The TUG test has been validated among older adults in the community [68]. The TUG test has been proven to be effective in assessing older adults at risk of falling, with a sensitivity and specificity of 87% [69]. The STS is reliable for various populations [70,71]. For the TUG test, participants will stand up from a standard armchair, walk at a normal pace for 3 m, return, and sit down again [72]. Participants who complete the TUG test in <12 seconds will be classified as having a low fall risk [73]. Then they will complete the STS. To begin, the participant should sit in the center of the chair, crossing their hands at the wrists and placing them on the opposite shoulder. They should keep their feet flat on the floor, their back straight, and their arms against their chest. Then, they should repeat the motion of standing up and sitting back down for 30 seconds. The results will be scored based on their age and sex as suggested by the CDC [2].

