Raw acceleration data from ActiGraph will be downloaded and converted to “.csv” files using ActiLife 6 Software (version 6.13.4; ActiGraph LLC). PA data will be processed using the R package *GGIR* (version 2.4-0). *GGIR* R package used to process multiday raw accelerometer data for PA research [103] includes (1) auto-calibration of acceleration signals according to local gravity [104], (2) detection of nonwear time, and (3) calculation of the average magnitude of dynamic acceleration corrected for gravity (ie, Euclidean Norm Minus One) over 5-second epochs and expressed in milli-gravitational units (mg) [105]. Nonwear time and sustained abnormally high accelerations will be imputed using the default settings [105]. The Euclidean Norm Minus One cut-off points will be used to estimate the total time spent in sedentary behavior, light intensity PA, and MVPA in participants.

For missing data treatment, the missing values will be imputed using the method of multiple imputations [106]. The maximum number of missing values within a scale will be based on the guidelines provided by the scale developers or based on a limit of 25% missing values. In the first analysis, all low-income older adults will be included according to their original group assignment [100]. Participants in the PEER group who completed at least 5 of the 8 group-based sessions will be included in the per-protocol analysis. Although every attempt will be made to ensure that low-income older adults complete all assessments, there may be some participant attrition over time. The missing data mechanism is assumed to be missing at random. The dropout patterns or missing data rates for the 2 arms will be examined to assess the differences. When possible, the models should be modified to account for relevant factors such as age, sex, general health perception, and the number of falls in the 6 months leading up to the baseline. To determine the impact of the PEER intervention during follow-up evaluations, the group-by-time interaction term will be incorporated into the model. Effect sizes (Cohen *d*) [107,108] will be calculated based on the estimated means and the pooled SD.

Aim 2 is to examine the effects of the intervention on FRA shifting and negative self-perceptions of aging.

The hypotheses are as follows:

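### Three primary outcomes, one of them with two measures, share a single .05 level, and nothing says how many must succeed

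*Protocol article*

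**What the plan says.** - **Primary outcomes.** Principal Findings lists "3 primary outcomes (fall risk, dynamic balance, and accelerometer-based PA"). The Primary Outcome Measures section has the same three entries: Fall Risk, Dynamic Balance and PA Measures.
- **Balance measures.** The Dynamic Balance section uses TUG and STS and argues for both: "It is important to conduct >1 balance test, as some participants may be identified as at risk on one and not another". No composite or combined score is defined.
- **Tests.** Data Analysis tests H 1.1 (fall risk) by a likelihood ratio test from a linear mixed model and continues: "the LRTs will be used to test hypotheses *1.2* and *1.3* for between-arm differences for dynamic balance and PA, respectively".
- **Level.** The same section states R as the software "for data analyses, with a significance level of" P=.05. It gives no split, order or lead outcome.
- **Sizing.** Power Analysis and Sample Size says that the estimate was "based on the primary outcomes of fall risk (CDC fall risk score) and PA (normalized MVPA") for aim 1. Dynamic balance does not appear there.
- **Activity variable.** Data Analysis derives "total time spent in sedentary behavior, light intensity PA, and MVPA" and does not repeat which of these tests H 1.3. Only the sample-size section points to normalized MVPA.

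**The concern.** With several primary tests at .05 each, the chance that at least one is falsely significant exceeds .05. Whether this matters depends on how the results become a conclusion. The article sets out to examine whether PEER is effective on its three primary outcomes, and Future Implications says what would follow if the intervention is effective. It never says what pattern of results would count as effective. As written, one nominally significant result among three or four could be reported as a positive trial, and so could a result on only one of the two balance tests. That choice would be open after the data are seen.

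**Working it through.** **The plan's own figures.** The article states no familywise error rate, so there is none to reproduce. It does show how .05 is used in one sizing statement: 120 per arm, P=.05 and 80% power give d=0.36 for the secondary outcomes. With n = 2(1.960+0.842)²/0.36², this needs 122 per arm, and power at 120 is 79.6%. So the full, undivided .05 was used there. In the sentence sizing the primary outcomes the value of alpha is absent from the text, possibly lost in extraction, so nothing is inferred from it.

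**Inputs**
- Number of tests k: 3 if dynamic balance is one test, 4 if TUG and STS are tested separately.
- Level per test: .05 (Data Analysis). A likelihood ratio test has no direction, so it is treated as two-sided.
- Correlation r between test statistics: not given. Assumed common to all pairs and varied from 0 to 0.9.
- Success rule: not given. Both any-one and all-must-succeed are shown.

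**Any one suffices, independent tests**
- Either direction: 1 − 0.95³ = 14.3%; 1 − 0.95⁴ = 18.5%.
- False benefit only, 2.5% each: 1 − 0.975³ = 7.3%; 1 − 0.975⁴ = 9.6%.

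**Any one suffices, correlated tests** (equicorrelated normal statistics, by numerical integration; simulation with 2,000,000 draws agrees to within 0.1 percentage point)

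| r | 3 tests, either direction | 4 tests, either direction | 3 tests, benefit only | 4 tests, benefit only |
|---|---|---|---|---|
| 0 | 14.3% | 18.5% | 7.3% | 9.6% |
| 0.3 | 13.6% | 17.4% | 6.8% | 8.7% |
| 0.5 | 12.5% | 15.6% | 6.3% | 7.8% |
| 0.7 | 10.9% | 13.0% | 5.5% | 6.5% |
| 0.9 | 8.4% | 9.4% | 4.2% | 4.7% |

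If only TUG and STS are correlated (0.3 to 0.9) and the rest are independent, four tests give 18.3% down to 16.1%.

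**All must succeed.** The error cannot exceed that of any single test, so it is at most 5%.

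**Within H 1.2 alone.** If either TUG or STS may carry the hypothesis, the error for that one hypothesis is up to 1 − 0.95² = 9.75% when independent.

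**Power after control.** A test with 80% power at two-sided .05 has expected statistic 1.960 + 0.842 = 2.802.
- Strictest Holm step, four tests (.05/4 = .0125, critical value 2.498): Φ(2.802 − 2.498) = 62%.
- Strictest Holm step, three tests (.05/3 = .0167, critical value 2.394): Φ(2.802 − 2.394) = 66%.
- All must succeed, each test at 80% power and independent: 0.8³ = 51% for three, 0.8⁴ = 41% for four.

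**The case against.** The strongest reply is that this is a condensed article, and that multiplicity rules are commonly left to an analysis plan that is not shown. H 1.1 to H 1.3 are also separate hypotheses. If each is concluded only on its own test, leaving .05 unadjusted is a debated but defensible choice. The article never says that one success is enough; its nearest sentence expects improvement on all outcome measures.

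Part of this stands. The any-one rule is an assumption, and the percentages depend on it. The sentence about all outcomes is an expectation, though, not a decision rule. The article also does more than stay silent: it fixes the primary outcomes, the test for each hypothesis and one level. Followed as written, those give the inflation shown unless a rule is added. The separate-hypotheses defence also does not settle H 1.2, which has two measures and no stated way to combine them.

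Three stronger readings are tempting but unsupported:
- A reader might take 16%-19% as a minimum. It is not: it needs four separate tests, correlations no higher than about 0.5 and the any-one rule. The article does not say outright that TUG and STS each get a primary test.
- A reader might count sedentary, light and MVPA time as three primary tests, making six in all (26.5% if independent). Those are outputs of the accelerometer processing, and the sample-size section names normalized MVPA as the PA variable.
- A reader might call the sample-size section a contradiction because it uses two of the three primaries. A trial may be sized on a subset of its primary outcomes, so this is a point to reconcile.

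**Conclusion.** The point holds in a conditional form. The article names three primary outcomes, tests them separately and states one level of .05, without saying what counts as success. Under an any-one rule and correlations from 0 to 0.5, the two-sided familywise error is 12.5%-14.3% for three tests and 15.6%-18.5% for four, roughly 2.5 to 3.7 times .05. At correlation 0.9 it is about 8%-9%. Counting only false claims in favour of PEER, the figures are about half of these, to be set against 2.5% for one test. If all must succeed, there is no inflation. The correlation, the any-one rule and the separate testing of TUG and STS are assumptions that the article neither states nor excludes. The weakness should be corrected because it bears on the trial's main claim and the remedy needs no new data.

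**What to change.** 1. Name one variable for each primary test: CDC fall risk score, TUG, STS and normalized MVPA. If TUG and STS are meant as one test, define how they are combined.
2. Make Power Analysis and Sample Size agree with Primary Outcome Measures and Principal Findings on which outcomes are primary, or say that the trial was sized on a subset.
3. Before outcome data are seen by arm, state one rule:
   - Holm over the named tests at an overall .05, with adjusted P values; or
   - a fixed sequence at .05 with the lead outcome named, for example one of the two on which the trial was sized; or
   - all primary tests must be significant at .05.

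**Cost.** The change is wording and a short calculation, with no added participants, visits or measurements. Enrollment was ongoing in August 2023, so the rule should carry a date. Each option has a price in power. Under Holm, a test with 80% power at .05 has about 62% at the strictest step with four tests and 66% with three; later steps are less strict. A fixed sequence costs the first test nothing, but no later test counts once an earlier one fails. Requiring all to succeed costs most, unless the outcomes are strongly correlated. These figures take 80% power per test as a starting point; among the primary outcomes the article claims it only for normalized MVPA.
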